## Study Outcomes

4

Participant data will be collected at the baseline assessment, within 1 week prior to surgery and at 6 weeks postoperatively. Programme measures are classified as (1) screening, (2) sample characteristics, (3) sleep outcomes, (4) clinical outcomes, and (5) physical fitness, anthropometric and patient‐reported measures (Appendix S7). A timeline of sleep health data collection and time points is shown in Table 2. This study is designed to make efficient use of participant time and minimise appointment burden by using standard prehabilitation assessment time points.

**TABLE 2 jsr70173-tbl-0002:** Timeline of sleep outcomes.

		T0	T1	—	T2
	Screening	Baseline	1 week preop	Surgery	6 week postop
Recruitment	×				
Attrition		×	×		×
Safety		×	×		×
Screening					
Global Sleep Assessment Questionnaire (GSAQ)	×				
Insomnia Severity Index	×				
STOP‐Bang Questionnaire	×				
Restless Legs Syndrome Diagnostic Index	×				
Sleep outcomes					
PSQI (primary outcome)		×	×		×
Sleep diary		×	×		×
PSP adherence*		×	×		
Sleep self‐efficacy scale		×	×		×

*PSP group only.

Eligibility rate will be measured as the number of patients eligible for the study divided by the number of patients screened for eligibility. Recruitment rate will be measured as the proportion of participants who are randomised divided by the number of identified eligible patients. Reasons for non‐participation will be collected. Reasons for, all or part of, the intervention not being delivered as intended will be recorded. The frequency of drop‐out during study participation will be documented including reasons. Any safety or adverse events related to the prehabilitation intervention will be reported during weekly telephone calls with participants. Reporting and grading will follow the Common Terminology Criteria for Adverse Events version 5.0 (U.S. Department of Health and Human Services 2017) Reporting of adherence to the PSP will be calculated as the number of sessions attended divided by the number of sessions stipulated in the protocol. In addition, the research member will record the number of BBTI components the participant adhered to as determined through discussion.

Demographic, physical fitness and anthropometric, clinical and patient‐reported outcomes are described in Appendix S7. Briefly, demographic characteristics will be documented via a standardised questionnaire. Physical fitness and anthropometric outcomes include the Six‐minute Walk Test (6MWT), short physical performance battery, timed up and go, grip strength, body mass index (BMI) and body composition via bioelectrical impedance analysis (mBCA 514, Seca, Hamburg, Germany). Clinical outcomes include hospital length of stay, readmission and surgical complications documented via patient medical record up to 90 days after surgery. Patient‐reported outcomes include the Edmonton Frail Scale (Rolfson et al. 2006) and Canadian Nutrition Screening Tool (CNST) (Laporte et al. 2015) administered at baseline and the PROMIS‐29+2 profile (Fries et al. 2009) administered at all timepoints.

Sleep health outcomes include the PSQI (Buysse et al. 1989) will be used to assess sleep health and is the primary outcome of this trial. The PSQI is a self‐report measure of sleep quality amongst seven subscales including subjective sleep quality, sleep latency, sleep duration, habitual sleep efficiency, sleep disturbances, sleep medication and daytime dysfunction. The scale's validity and reliability have been determined amongst clinical and older adult populations (Spira et al. 2012; Carpenter and Andrykowski 1998). The GSAQ (Roth et al. 2002) will be used to screen for sleep disorders. A previous systematic review (Klingman et al. 2017) identified the GSAQ as the most suitable screening tool for multiple sleep disorders due to its efficiency and comprehensiveness. The Insomnia Severity Index (ISI) will be used to screen for insomnia, the most common sleep disorder. The validity and reliability of the ISI have been previously established (Bastien et al. 2001). The STOP‐Bang Questionnaire will be used to screen for obstructive sleep apnea. The validity and reliability of this instrument have been previously established in surgical patients (Chung et al. 2016). The Restless Legs Syndrome Diagnostic Index (RLS‐DI) will be used to screen for Restless Legs Syndrome (Beneš and Kohnen 2009). This scale has been previously validated with high sensitivity and specificity to screen for Restless Legs Syndrome (cut‐off score > 11). The sleep self‐efficacy scale (SES) measures confidence in sleep behaviour change (Lacks 1987). Self‐efficacy has previously been determined as one of the most significant predictors of adherence to a behavioural intervention for improving sleep (Bluestein et al. 2011). A participant sleep diary will be used to record sleep for 1 week at each study time point (Carney et al. 2012). The sleep diary will be available in hard copy, or a virtual copy may be emailed to the participant if requested. The questions will be based on a subset of questions available online at https://consensussleepdiary.com/.

All participants will be provided with a Fitbit Inspire 3, a small non‐intrusive and waterproof wrist‐worn device that uses actigraphy to measure orientation and movement and uses photoplethysmography (PPG) to detect periodic changes in blood flow beneath the sensor; thereby measuring changes in heart rate. The activity tracker measures sleep–wake activity to determine time in bed, sleep duration, nighttime awakenings and physical activity levels. The heart rate monitor will measure resting heart rate and heart rate variability, metrics of overall fitness and autonomic nervous system function that have previously been found to be correlated with sleep (Sajjadieh et al. 2020). The device's predecessor was validated against polysomnography demonstrating high sensitivity (93.9%) and low specificity (13.1%), with an accuracy of 76% (Lim et al. 2023).

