### Randomisation and Blinding

3.5

Participants will be randomised 1:1 (PSP+PREHAB: PREHAB) using a computer‐generated randomisation sequence. This randomisation process will be blinded such that the research team member who generates the randomisation sequence is not in contact with interventionists, outcome assessors or the participant's circle of care. Due to the nature of the study, participant and interventionist (PSP) blinding is not possible. However, outcome assessors and clinicians delivering PREHAB will be blinded to group allocation.

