### Standard of Care Prehabilitation (PREHAB)

3.6

All participants (both study arms) will receive standard of care multimodal prehabilitation (PREHAB) from consent until surgery. All participants will undergo a baseline assessment consisting of a verbal interview and physical function assessment to ascertain medical history, functional capacity and relevant information required to individualise PREHAB (Table 1). The PREHAB model of care has been published previously (Randall et al. 2024). PREHAB consists of exercise prehabilitation and nutritional prehabilitation for all participants. Psychological and smoking cessation prehabilitation is delivered to patients screening positive using standardised screening tools. Prehabilitation modalities are summarised below and detailed in Appendix S4.

**TABLE 1 jsr70173-tbl-0001:** PREHAB baseline assessment.

Assessment component	Description
Health history and intervention needs screen	Comorbidity collection (CCI), Frailty (Edmonton Frail Scale; EFS), Nutrition risk via the CNST Sleep via the Global Sleep Assessment Questionnaire (GSAQ).
Body composition	Body mass in kilogrammes using a standing digital scale Height in centimetres using a wall‐mounted stadiometer Body mass index (calculated) body fat %, lean mass and fat mass measured with the mBCA 514 (Seca, Hamburg, Germany)
Functional capacity	Grip strength via hand grip dynamometer Timed up and go Short physical performance battery Six‐minute walk test

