### Analytic Plan

4.1

All data will be collected and imported into R version 4.1.2 for statistical analysis; an alpha of 0.05 will be used. Participant characteristics will be summarised using means (SD) or medians [IQR] for continuous variables and frequency (%) for categorical variables. We will report reasons for exclusion and attrition, as well as safety or adverse events with frequency and percentages.

The statistical analysis plan was created in consultation with a UHN biostatistician. The primary outcome (PSQI score) will be compared between the two treatment arms using analysis of covariance (ANCOVA), controlling for baseline PSQI score. A linear mixed effects model will be used to compare treatment arms with respect to the longitudinal PSQI scores (baseline, preoperative, 6 weeks post‐surgery). Point estimates and 95% confidence intervals will be calculated for changes in the PSQI between groups at each timepoint. We will use Q–Q plots and histograms to assess data normality. If non‐normality is encountered and cannot be corrected through data transformations (e.g., log, square root), we will employ appropriate non‐parametric alternatives, such as the Mann–Whitney U test for between‐group comparison. Model assumptions including homogeneity of variance (Levene's Test) and normality of dependent variables (Shapiro–Wilk Test) will be used. Independence of observations was assessed using the Durbin Watson (DW) statistic, with values between 1.5 and 2.5 indicating independence. Sensitivity analyses will address potential loss to follow‐up by replacing the missing outcome measurements with best or worst values to assess the robustness of our results. In the unlikely event of unbalanced baseline characteristics between the treatment arms, the mixed effects models will be adjusted for these potential confounders (e.g., age, sex, etc.). Conclusions will be drawn using comparisons of each time point between groups. The minimum clinically important difference for the PSQI score will be 1.3 based on previous research (Shergis et al. 2016). Given a lack of consensus for the PSQI MCID, previous research has interpreted any statistically significant change in the PSQI to be clinically meaningful (Shergis et al. 2016).

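### The stated adverse-event rule sets a relatedness condition at capture, so recorded event frequencies could differ between arms through attribution rather than event rates

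*Protocol article*

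**What the plan says.** All references are to the protocol article.

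- **Collection** (section 4, Study Outcomes): "Any safety or adverse events related to the prehabilitation intervention will be reported during weekly telephone calls with participants". On severity, "Reporting and grading will follow the Common Terminology Criteria for Adverse Events version 5.0".
- **Timing** (Table 2): safety is marked at baseline, 1 week before surgery and 6 weeks after surgery.
- **Analysis** (section 4.1, Analytic Plan): the authors will report reasons for exclusion and attrition, "as well as safety or adverse events with frequency and percentages". No relatedness limit appears here, and no between-arm test of safety is stated.
- **Blinding** (section 3.5): "participant and interventionist (PSP) blinding is not possible", but "outcome assessors and clinicians delivering PREHAB will be blinded to group allocation".
- **Treatment** (sections 3.6 and 3.7): both arms "will receive standard of care multimodal prehabilitation (PREHAB) from consent until surgery"; the intervention arm also receives PSP in four weekly sessions.
- **Record-based outcomes** (section 4): "Clinical outcomes include hospital length of stay, readmission and surgical complications documented via patient medical record up to 90 days after surgery".

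**The concern.** A relatedness judgement is useful as a label on an event already recorded. As a condition for recording it, it decides what enters the data, and later grading or analysis cannot bring back what was left out.

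Here the condition has no clear referent. Both components carry the word prehabilitation in their names, so the phrase could mean PREHAB, PSP or the pair. Only one arm has PSP to attribute an event to, and participants, who are the source of the call reports, know which arm they are in.

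What is at stake is the description of harms, not the primary analysis. Participants are referred for elevated surgical risk, mostly because of frailty (section 3.2). The main PSP component includes reduced time in bed (section 3.7), and the Discussion acknowledges that no formal feasibility trial has been published. Event frequency in the PREHAB-alone arm is the natural background for judging whether PSP adds harm. A filter at capture removes part of that background, possibly by a different amount in each arm.

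**Working it through.** The document gives no adverse-event rate, safety margin or safety power, so there is no figure to reproduce. The check sets the passages side by side and then illustrates the possible size with assumed inputs.

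**1. What the condition could mean**

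| Reading of the condition | PSP + PREHAB arm | PREHAB arm |
|---|---|---|
| Related to PREHAB only | PSP-related events fall outside the rule | PREHAB-related events captured |
| Related to PREHAB or PSP | Two possible causes to attribute an event to | One possible cause |

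Under the first reading, harms of the component being tested are not covered. Under the second, the same event, such as daytime fatigue, can qualify in one arm through a cause that does not exist in the other. Neither reading ensures that recorded frequencies are comparable.

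**2. Who could apply the condition**

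The article does not say who makes the calls or who decides whether an event is related. A caller who knows the arm applies the condition unblinded. A blinded caller cannot readily judge relation to PSP without learning whether the participant received it. Assessor blinding therefore does not by itself settle the matter.

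**3. What the other safety data cover**

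Readmission and surgical complications are taken from the record after surgery, whatever the cause. PSP is delivered before surgery, in patients whose operation is 4–12 weeks from consent (section 3.2). Non-surgical events in that window are not systematically covered by those outcomes, so for them the weekly-call rule is the stated route.

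**4. Possible size**

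Inputs from the document: 154 participants (section 3.3) and "Participants will be randomised 1:1" (section 3.5), so 154 / 2 = 77 per arm.

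Assumed inputs: true event risk *r*, equal in both arms, and share of events judged related and so recorded, *a* in one arm and *b* in the other.

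Recorded risk = *r* × share. Apparent ratio = (*r* × *a*) / (*r* × *b*) = *a* / *b*, whatever the value of *r*.

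| *r* | *a* vs *b* | Recorded risk | Expected participants of 77 | Apparent ratio |
|---|---|---|---|---|
| 20% | 50% vs 50% | 10% vs 10% | 7.7 vs 7.7 | 1.0 |
| 20% | 50% vs 40% | 10% vs 8% | 7.7 vs 6.2 | 1.25 |
| 20% | 50% vs 25% | 10% vs 5% | 7.7 vs 3.9 | 2.0 |
| 10% | 50% vs 25% | 5% vs 2.5% | 3.9 vs 1.9 | 2.0 |
| 40% | 50% vs 25% | 20% vs 10% | 15.4 vs 7.7 | 2.0 |

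The error can also run the other way. If the true risk were 40% with PSP and 20% without, and the shares were 25% and 50%, the recorded risks would be 40% × 25% = 10% and 20% × 50% = 10%, which hides a true doubling.

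The apparent ratio is the ratio of the assumed shares. The table shows how the mechanism works; it is not evidence that the shares will differ.

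**The case against.** The strongest reply is that this is one sentence in a condensed article, and that several stronger conclusions a reader might draw from it are not supported.

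- **That only related events are recorded anywhere.** The sentence says what the calls will report and does not exclude other records. The Analytic Plan and Table 2 carry no relatedness limit, and the 90-day outcomes are collected whatever the cause. This stands: the document supports saying that the stated rule is limited, not that all other events are lost.
- **That the trial is unblinded.** It is not. Outcome assessors and PREHAB clinicians are blinded; participants and PSP interventionists are not.
- **That people who know the arm judge relatedness.** The article does not say who judges it. Only the open status of the reporting participants is established.
- **That the extra PSP sessions inflate reporting.** Nothing makes those sessions a route for adverse events, and the calls are not restricted by arm. The documents do not establish unequal contact for safety reporting.
- **That Table 2 contradicts the weekly calls.** Safety marks at assessments can coexist with calls between them.
- **That a safety comparison is planned and will be wrong by a factor of two.** No between-arm test is stated, and the factor of two is an assumed input. A summary by arm is a fair expectation in a two-arm trial, but it is implied rather than stated.

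Scripts, forms and the identity of an assessor can reasonably be left to the full protocol, and their absence is not the point. What remains is a rule the article does state: the relatedness condition sits at capture, its referent is unclear, and the record-based outcomes do not fill the preoperative period.

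**Conclusion.** The point holds in a limited form and is worth correcting. Followed as written, the rule lets attribution decide which preoperative adverse events enter the data, and the frequencies in the Analytic Plan would inherit that. A difference between arms could then reflect attribution, and events not recognised as related need not be captured. Readmissions and surgical complications to 90 days are not affected, nor is the primary PSQI analysis.

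The size is unknown. It depends on whether the share of events judged related differs by arm: no difference leaves the ratio undistorted, and the assumed shares shown above multiply it by 1.25 or 2.0. The conclusion assumes that the calls are run as the sentence says and that no wider capture rule exists in the full protocol, which is not shown. If such a rule exists, the article's sentence needs only to be brought into line with it.

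**What to change.** In Study Outcomes:

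1. Delete the relatedness condition from the collection sentence.
2. Record all adverse events in both arms, with the same question, at the contacts already planned: the weekly calls and the Table 2 safety time points.
3. Keep CTCAE v5.0 for grading.
4. Classify relatedness afterwards in a separate field, once for PREHAB and once for PSP, blinded to allocation where that is possible.

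In the Analytic Plan, state that all events and related events will both be tabulated by arm, as frequencies and percentages.

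The cost is a short wording change and slightly more data entry, with no new contacts. It should be made before data collection has gone far, because events left unrecorded during the calls cannot be reliably reconstructed later.

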### Analytic Plan

4.1

All data will be collected and imported into R version 4.1.2 for statistical analysis; an alpha of 0.05 will be used. Participant characteristics will be summarised using means (SD) or medians [IQR] for continuous variables and frequency (%) for categorical variables. We will report reasons for exclusion and attrition, as well as safety or adverse events with frequency and percentages.

The statistical analysis plan was created in consultation with a UHN biostatistician. The primary outcome (PSQI score) will be compared between the two treatment arms using analysis of covariance (ANCOVA), controlling for baseline PSQI score. A linear mixed effects model will be used to compare treatment arms with respect to the longitudinal PSQI scores (baseline, preoperative, 6 weeks post‐surgery). Point estimates and 95% confidence intervals will be calculated for changes in the PSQI between groups at each timepoint. We will use Q–Q plots and histograms to assess data normality. If non‐normality is encountered and cannot be corrected through data transformations (e.g., log, square root), we will employ appropriate non‐parametric alternatives, such as the Mann–Whitney U test for between‐group comparison. Model assumptions including homogeneity of variance (Levene's Test) and normality of dependent variables (Shapiro–Wilk Test) will be used. Independence of observations was assessed using the Durbin Watson (DW) statistic, with values between 1.5 and 2.5 indicating independence. Sensitivity analyses will address potential loss to follow‐up by replacing the missing outcome measurements with best or worst values to assess the robustness of our results. In the unlikely event of unbalanced baseline characteristics between the treatment arms, the mixed effects models will be adjusted for these potential confounders (e.g., age, sex, etc.). Conclusions will be drawn using comparisons of each time point between groups. The minimum clinically important difference for the PSQI score will be 1.3 based on previous research (Shergis et al. 2016). Given a lack of consensus for the PSQI MCID, previous research has interpreted any statistically significant change in the PSQI to be clinically meaningful (Shergis et al. 2016).

Additional exploratory analyses using linear mixed effect models will be conducted to understand the effect of the intervention on secondary outcomes that are measured longitudinally, including physical fitness (e.g., 6MWT) outcomes and the PROMIS‐29+2. For outcomes that are measured at only one time point (e.g., length of hospital stay), we will use non‐parametric Wilcoxon signed‐rank *t*‐tests or Chi‐square tests for continuous and categorical outcomes, respectively. Given the exploratory nature of secondary outcomes, *p*‐values will be adjusted using Bonferroni corrections to account for multiple comparisons. All analyses will be conducted using the intention to treat principle. The data will be reported in accordance with the Consolidated Standards of Reporting Trials (CONSORT) guidelines for reporting randomised trials (Schulz et al. 2010).

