### Sample Size

3.3

A total of 154 participants will be recruited for this study. The sample size was computed by a biostatistician at UHN for an ANCOVA design in which the Pittsburgh Sleep Quality Index (PSQI) score will be compared between the two arms at the preoperative timepoint, controlling for baseline scores. Assuming a PSQI score mean of 11.9 (SD 2.6) points for the usual care arm (Atoui et al. 2023) with no correlation between baseline and preoperative scores, a sample size of 64 participants per arm (128 total) will be required to detect a difference in mean PSQI score of 1.3 points, which is the minimum clinically important difference (Longo et al. 2021). This difference between the two arms corresponds to a Cohen's d effect size of 0.5 with 80% power and an alpha of 0.05. The final sample accounts for 20% attrition.

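### A normality check on the outcome, not the residuals, can move the primary PSQI analysis off baseline-adjusted ANCOVA, and the named fallback loses both baseline PSQI and the 1.3-point scale

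*Protocol article*

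**What the plan says.** All of this is in the Protocol article, Analytic Plan (section 4.1), unless noted.

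- The primary comparison of PSQI is an "analysis of covariance (ANCOVA), controlling for baseline PSQI score".
- Normality is to be examined with Q–Q "plots and histograms to assess data normality".
- The next sentence gives the consequence. If non-normality is "encountered and cannot be corrected through data transformations (e.g., log, square root), we will employ appropriate" non-parametric alternatives; the Mann–Whitney U test is the only example named.
- A later sentence lists formal assumption checks: Levene's test for variances, and Shapiro–Wilk for "normality of dependent variables". No consequence is attached to either.
- "Independence of observations was assessed using the Durbin Watson (DW) statistic", with a range of values taken to indicate independence and no action if the value falls outside it.
- The section also sets 1.3 points as the minimum clinically important difference. It promises point estimates and 95% confidence intervals for between-group PSQI changes at each timepoint.

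Sample Size (section 3.3) designs the trial as an ANCOVA with 64 per arm to detect 1.3 points at SD 2.6, assuming zero correlation between baseline and preoperative scores.

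The primary outcome is not exempted from the switching rule.

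**The concern.** Three features of the rule are poor choices for a primary analysis.

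1. **Wrong quantity.** ANCOVA and the linear mixed model assume approximately normal residuals. The marginal distribution of the score is not the assumption. An integer score can fail a formal test on its raw values while the model's residuals are unremarkable.
2. **Changed target.** Mann–Whitney U compares distributions by rank and takes no covariate, so baseline PSQI goes. A log analysis gives a ratio and a square-root analysis a difference in mean roots. None of these is a mean difference in PSQI points, which is what the sample size and the 1.3-point threshold refer to.
3. **Open choice.** The visual check has no criterion. Up to four primary analyses remain possible (raw, log or square-root ANCOVA, or a rank test), to be settled once outcome data are in hand.

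At stake are the interpretability of the primary result and, if baseline and preoperative scores correlate, some of the power that baseline adjustment would provide.

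**Working it through.** **Inputs.** From Sample Size: usual-care mean 11.9, SD 2.6, difference 1.3, 64 per arm, correlation 0. From Analytic Plan: alpha 0.05 (taken as two-sided). Assumed, because the documents do not state it: PSQI is an integer from 0 to 21. The bounds matter little, since 11.9/2.6 = 4.6 SD and (21 − 11.9)/2.6 = 3.5 SD. The integer scoring drives the result.

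**The plan's own figure.** n per arm = 2(1.960 + 0.842)² × 2.6²/1.3² = 2 × 7.85 × 4 = 62.8, so 63. The t-based version gives 63.8, so 64, with power 0.801. The stated 64 is reproduced.

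**How often would a formal normality test fail well-behaved scores?** Scores were drawn as normal, rounded and clipped to 0–21, and tested by Shapiro–Wilk at 0.05 (10,000 replicates; 5,000 for the ANCOVA comparisons).

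| What is tested | Rejects |
|---|---|
| Both arms pooled, 2 × 64, 1.3-point difference | 57% |
| Either arm, 64 each | 40% |
| One arm of 64 | 23% |
| Pooled N = 128, no difference, SD 2.0 / 2.6 / 3.0 / 3.5 / 4.0 | 99 / 63 / 37 / 21 / 16% |
| Raw, log and square root all reject, 2 × 64 | 49–52% |
| Unrounded normal scores, pooled 2 × 64 | about 4–5% |
| ANCOVA residuals, correlation 0 | about 9% |
| ANCOVA residuals, correlation 0.3–0.7 | about 5–6% |

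The excess comes from integer scoring: the same data unrounded reject at the nominal rate. In this setting transformation rarely removes the failure.

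**What does dropping baseline cost in power?** ANCOVA's residual SD is 2.6 × √(1 − ρ²): 2.60, 2.48, 2.25 and 1.86 at ρ = 0, 0.3, 0.5 and 0.7. Approximate power is Φ(1.3/(residual SD × √(2/64)) − 1.96). At ρ = 0 this is Φ(2.83 − 1.96) = 0.81, and at ρ = 0.5 it is Φ(3.27 − 1.96) = 0.90. Simulation on rounded scores gives slightly lower values:

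| ρ | ANCOVA | Mann–Whitney |
|---|---|---|
| 0 | 0.80 | 0.78–0.79 |
| 0.3 | 0.83 | 0.78 |
| 0.5 | 0.88–0.89 | 0.77–0.78 |
| 0.7 | 0.97 | 0.77–0.78 |

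Mann–Whitney power does not change with ρ because it ignores baseline.

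**Does the switch inflate false positives?** No. With a Shapiro–Wilk switch imposed, the type I error was 4.7–5.1% over ρ = 0, 0.3, 0.5 and 0.7 (3,000 trials per setting).

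**Can the fallback be read against 1.3 points?** On the log scale, moving from 11.9 to 10.6 is a ratio of 10.6/11.9 = 0.891. For a patient at 8 points the same ratio is 8 × 0.109 = 0.87 points. One ratio therefore maps to different point changes, and a rank statistic maps to none.

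**The case against.** **Shapiro–Wilk is not the stated trigger.** The conditional follows the sentence on Q–Q plots and histograms; Shapiro–Wilk comes later with no action attached. A reader might infer that the trial would switch tests about half the time. The document does not support that. Under a visual check the simulated scores look normal (median Q–Q correlation 0.99, absolute skewness above 0.5 in about 2% of trials), and an analyst would usually keep ANCOVA. This objection stands, so the rejection rates are conditional and must be given as a range.

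**The power loss is against a bonus, not the plan.** The sample size takes no credit for baseline correlation. At ρ = 0 the loss is about a percentage point, and even at ρ = 0.5 Mann–Whitney keeps 77–78%, close to the planned 80%. This stands too: the documents do not support a claim that the fallback leaves the trial clearly underpowered.

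**No false-positive problem is shown.** Choosing a test after a look at the data invites the inference that alpha is inflated. The simulations show about 5%.

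**The fallback is an example and comes last.** Transformation precedes it, the wording does not exclude a baseline-adjusted rank method, and an analysis plan not shown may say more. This stands in part. But the only fallback named is unadjusted, and the rule is written into the article, so it is not merely an omitted detail.

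**Point estimates are promised anyway.** A points-scale estimate could still be reported, but it would not correspond to the test carrying the primary conclusion.

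**Conclusion.** The concern holds in limited form and is a should-fix. The plan aims its normality check at the data or dependent variable, and lets that check move the primary analysis to a scale or test that no longer estimates the mean difference the trial was sized to detect. The named fallback also discards baseline PSQI.

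The case rests on interpretability and on fixing the primary analysis in advance. It does not rest on error rates, since type I error is about 5% throughout. The power cost runs from negligible at the protocol's planning correlation of 0 to roughly 20 percentage points at 0.7. The Shapiro–Wilk rates (57%, 40% or 23% at SD 2.6 depending on what is tested; 16% to 99% pooled across SDs of 4.0 to 2.0) apply only if that test informs the switch, and only for rounded-normal integer scores.

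Durbin–Watson is a side point. It is uninformative for patients in arbitrary row order, and repeated measures on one patient are dependent by design. A reader might think it could alter the primary analysis, but no consequence is attached to it.

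**What to change.** In Analytic Plan (section 4.1), before outcome data are examined:

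- State that ANCOVA on untransformed PSQI, adjusted for baseline, is the primary analysis whatever the normality checks show.
- Direct the checks at model residuals, by plots, and remove the Shapiro–Wilk test on the dependent variable for this outcome.
- If residuals look poor, report HC3 or bootstrap confidence intervals for the same adjusted mean difference.
- If a rank-based check is wanted, name baseline-adjusted rank ANCOVA as a sensitivity analysis.
- Delete the transformation and Mann–Whitney switch for the primary outcome.
- Optionally drop the Durbin–Watson check.

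The cost is a few sentences of wording. No patients, visits or data items change.

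### At the planned 20% attrition, the under-specified best-or-worst filling of missing PSQI scores cannot tell a robust 1.3-point effect from a fragile one

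*Protocol article*

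**What the plan says.** Section 4.1 (Analytic Plan) of the protocol article makes the primary analysis an ANCOVA of PSQI adjusted for baseline. It adds a linear mixed model over the baseline, preoperative and 6-week scores. For loss to follow-up it names one approach, a sensitivity analysis "replacing the missing outcome measurements with best or worst values to assess the robustness of our results". The direction of the fill in each arm and the values to be used are not given. The same section states: "All analyses will be conducted using the intention to treat principle".

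Section 3.3 (Sample Size) supplies the planning figures: "Assuming a PSQI score mean of 11.9 (SD 2.6) points for the usual care arm", "with no correlation between baseline and preoperative scores", a target difference of 1.3 points, 64 evaluable participants per arm and 154 recruited. It adds: "The final sample accounts for 20% attrition".

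**The concern.** A sensitivity analysis should show how far the missing scores would have to depart from the main assumption before the conclusion changes. Extreme-value filling answers a cruder question. The shift it produces depends only on the share missing and the distance between the fill values. It is the same whether the participants who were lost did well or badly. If that shift is several times the target effect, failure is built in. If the fill direction is left open, the same data can give very different answers.

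The risk of uneven dropout is realistic here. Participants know their allocation, the outcome is self-reported, and only the PSP+PREHAB arm carries four extra sessions. A reader will want this check to be informative.

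**Working it through.** **Inputs.** From section 3.3: PREHAB mean 11.9, SD 2.6, difference 1.3 (so a PSP+PREHAB mean of 10.6), zero baseline correlation, 20% attrition, 154 recruited (77 per arm). The article does not give the PSQI range or its direction. I assume that higher is worse and try three pairs of best (B) and worst (W) values:

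- 0 and 21, as assumed scale limits
- 6.7 and 17.1, which is 11.9 ± 2 × 2.6
- 8.65 and 13.85, which is 1 SD either side of 11.25, the midpoint of the two arm means

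**The plan's own figure.** 2 × (1.96 + 0.84)² × (2.6/1.3)² gives 63 per arm by the normal approximation. The t-test version gives 63.8, so 64 per arm reproduces. 128 × 1.2 = 153.6, so 154 reproduces. If 20% of 154 are lost, 154 × 0.8 = 123 remain and power is about 79%.

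**Formulas.** Let d be the share missing, unrelated to outcome. In an arm with mean m filled with value v:

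- filled mean = (1 - d)m + dv
- filled variance = (1 - d)SD² + d(1 - d)(m - v)²

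Differences are PSP+PREHAB minus PREHAB. Opposite fills give -(1 - d) × 1.3 ± d(W - B). The same fill in both arms gives -(1 - d) × 1.3.

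**Worked case (0 and 21, d = 0.20, adverse).** PSP+PREHAB: 0.8 × 10.6 + 0.2 × 21 = 12.68. PREHAB: 0.8 × 11.9 + 0.2 × 0 = 9.52. Difference: +3.16. The variances are 22.71 and 28.07, so SE = √(50.78/77) = 0.81 and the 95% CI is 1.57 to 4.75.

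**All cases at 20% missing per arm:**

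| B, W | PSP+PREHAB worst, PREHAB best (95% CI) | Reverse (95% CI) | Same fill in both arms | Power, same fill |
|---|---|---|---|---|
| 0, 21 | +3.16 (1.57 to 4.75) | -5.24 (-6.69 to -3.79) | -1.04 | 25% best, 29% worst |
| 6.7, 17.1 | +1.04 (-0.01 to 2.09) | -3.12 (-4.06 to -2.18) | -1.04 | 59% best, 50% worst |
| 8.65, 13.85 | 0.00 (-0.84 to 0.84) | -2.08 (-2.85 to -1.31) | -1.04 | 71% |

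**Where the effect disappears.** The adverse fill cancels 1.3 points when d = 1.3/(1.3 + W - B). That is 5.8%, 11.1% and 20% for the three ranges. Significance of an exact 1.3-point difference goes earlier, at about 1.7%, 3.7% and 7.2% missing, or roughly 1, 3 and 6 participants per arm. At 20% missing, the difference must exceed 0.25 × (W - B) merely to keep its sign: 5.25, 2.6 and 1.3 points.

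**Other attrition.** 154 leaves 128 only if about 17% are lost. At 16.7% the adverse fills give +2.42, +0.65 and -0.21, and the last has a 95% CI of -1.06 to 0.63. With unequal loss (15% PREHAB, 25% PSP+PREHAB) and 21 in both arms, the result is (0.75 × 10.6 + 0.25 × 21) - (0.85 × 11.9 + 0.15 × 21) = 13.20 - 13.265 = -0.065. So the same fill in both arms is mild only when attrition is equal.

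**The case against.** The strongest defence is that the plan commits to none of the severe cases. It does not say that the fills are opposite or at scale limits. With the same fill and equal attrition the estimate shrinks by a fifth and is not overwhelmed. Also, 20% is a planning allowance, not a forecast of missing preoperative scores. With far fewer missing, or a larger effect, bounds that still exclude zero would be convincing evidence. All of that stands and limits the point to the planned attrition and effect. It does not rescue the wording, because the open choice lets one dataset yield -5.24, -1.04 or +3.16.

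The planned mixed model already gives a missing-at-random estimate at each time point. That also stands, but it does not test departures from missing at random.

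Three stronger readings are tempting, and the article does not support them:

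- **The primary ANCOVA drops everyone without a preoperative score, against intention to treat.** A single-time-point ANCOVA with no named imputation invites that inference, but no sentence says so. The handling may be in an analysis plan that is not shown.
- **An ineffective intervention could be declared effective.** With a zero true effect, the favourable 0-21 fill does give 0.20 × 21 = 4.2 points in its favour. But that is one bound read alone, and the plan presents the filling as a robustness check, not as a basis for claiming efficacy.
- **Those who leave the sleep sessions sleep worse.** The article gives no evidence for this, and missing a session is not the same as missing a PSQI score.

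**Conclusion.** The point holds for the sensitivity analysis and goes no further. At 20% missing and a true difference of 1.3 points, opposite fills put the two bounds on either side of zero for the two wider ranges. At 1 SD the adverse bound is exactly zero. The conclusion therefore does not depend on the assumed 0-21 range. The same fill in both arms gives -1.04, with power of 25-59% for the wider ranges and 71% at 1 SD, against about 79% for the 123 observed. At the planned values a failed check says little about the missing scores themselves.

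These results assume the planning mean and SD, zero baseline correlation, loss unrelated to outcome and, except where stated, equal loss in the two arms. The primary estimate is unaffected. Nothing here shows that the ANCOVA is the wrong primary analysis. Moving to the mixed model would be a preference, since it gains little at the preoperative visit from participants lost before surgery.

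**What to change.** Keep the ANCOVA as primary and change only the sensitivity analysis:

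1. Use multiple imputation followed by the ANCOVA as the missing-at-random base case.
2. Worsen the imputed PSP+PREHAB scores in steps of 0, 0.5, 1.0 points and so on. Report the shift at which the conclusion changes, set against 1.3.
3. Add a reference-based run in which PSP+PREHAB dropouts are imputed as if they followed the PREHAB arm.
4. Report the preoperative contrast from the planned mixed model as a supportive missing-at-random estimate.
5. If best-or-worst filling is kept, label it an outer bound and state the fill values and their direction in each arm.

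This gives a readable scale. At 20% missing, each 0.5-point step moves the difference by 0.2 × 0.5 = 0.10. From -1.3 with SE 2.6 × √(2/61.6) = 0.47, the upper confidence limit is -1.3 + 0.92 = -0.38. Significance would then be lost at a shift of about 0.38/0.2 = 1.9 points, if the SE is taken as unchanged. Readers can judge whether dropouts that much worse are plausible.

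The cost is a little more analysis code and a few sentences in the plan, settled before unblinding. No new data are needed. The downside is a missing-at-random base case, which the delta steps then test.
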